### Intervention Group

#### Week 1: Psychoeducation and Test Diary

After baseline assessments, a few days later in the same week, the test persons participate in individual 1-h psychoeducation sessions about circadian clocks and their effects on health and psychiatric disorders, such as addiction and depression. The scientific content is communicated in simple language. Firstly, the participants get explained that circadian rhythms can be found virtually everywhere in nature and that they have impact on essentially all physiological processes, including sleep-wake cycles, hunger, digestion, wound healing, cellular functions, and molecular processes. A focus is on their involvement in neurobiological systems, such as reward, addiction networks, and behaviors. During the session, the test subjects are led to understand how important regular daily routines are for mental and physical health. Therefore, the study assistant emphasizes the importance of certain environmental cues that can serve as *Zeitgebers*, such as light and food. Together with the participants, the impact of light on sleep is discussed and how light can be avoided at late hours (e.g., by stopping the use of mobile phones, watching TV, or playing computer games after sunset or by using blue-light filters). Furthermore, the importance of regular mealtimes is discussed as food is an important *Zeitgeber* for many organs, including brain areas involved in the development of addiction. At the end of this session, the study assistant hands out a circadian diary (Supplementary Table 1), which the participant is asked to fill out for 1 week. With the help of the diary, data on times of meals, snacks, activity times, sleep duration, sleep quality, mood, and alcohol craving are collected on a daily basis. At this point in time, the test persons do not yet receive any concrete instructions as to when they should execute activities. Rather, they are instructed to use the following days to see if they can recognize certain temporal patterns in their own behavior and to consciously follow these patterns. Filling out the test diary serves on the one hand to create an awareness of their own daily rhythms. Besides, it gives the test persons the opportunity to familiarize themselves with the filling out of the diary. On the other hand, the data obtained on eating and sleeping times can be used in the next session as a basis for drafting a daily structure plan.

#### Week 2: Establishment of a Daily Structure Plan

After 1 week, participants are invited for another individual session. During this session, the entries of the test diary are discussed and a personalized daily structure plan for eating and sleeping times and, if desired by the test subjects, times for leisure activities such as sports is created together with the participants. For each subject, a balance is attempted between endogenous circadian preferences and time constraints imposed by the environment, which the subjects may not be able to influence. Thus, it is sought to adapt all possible freely selectable times to the personal preferences given by individual circadian characteristics. However, some test persons are embedded in certain rigid daily structures on some days (e.g., due to working hours). These restrictive environmental factors are also taken into account when creating the daily structure plan in order to ensure their realistic implementation in everyday life and to avoid possible sleep deprivation due to late bed and early work hours. If this is the case, it is recommended to the test persons to strictly adhere to the daily schedule of working days even on non-working days in order to avoid repeated shifts in the circadian system and to maintain a maximum of regularity, and therefore endogenous synchronization. However, for each individual subject, it must be checked whether the daily schedule created for them deviates significantly from their endogenous circadian preferences and thus leads to a permanent misalignment between endogenous and exogenous rhythms or sleep deprivation. If the discrepancy is larger than 2 h, a specific adjustment of the lighting conditions is recommended, e.g., for late chronotypes with early work hours, increasing the light in the morning (bright light therapy) to advance the circadian system and to promote wakefulness, and decreasing it in the evening to further support the phase advance and promote tiredness.

Furthermore, at this meeting the test persons are again made aware of the importance of very regular eating and sleeping times. If the test diary shows that the test person has lived rather irregularly, solutions are developed for maintaining more daily regularity. This session also serves as an opportunity to answer potential questions from the study participants and to remind them of the importance of adhering to the daily structure plan that has been drawn up. Participants receive new blank diaries which they are asked to fill in for the next 4 weeks. The times of the designed daily structure plan are handwritten in the empty diary pages as a visual support for precise adherence to the times.

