**Figure 1 F1:**
[figure not shown]
Procedure of the DAILY study. Patients are screened and recruited by a member of the study staff. After 1 day at the earliest the participants sign the consent form. On this day, they are informed about the contents of the study; the contents discussed differ between intervention and control group. In addition, questionnaires are filled out and blood is drawn. During the week, a psychoeducation session takes place in which the contents and the aims of the study are deepened, further questionnaires (Table 1) are filled in, and a test diary is handed out to record times of daily actions which act as *Zeitgebers*. After at least 1 week, the diary is evaluated and a daily structure plan for regular exposure to *Zeitgebers* is worked out together with the test persons, to which they should adhere for the next 4 weeks. Subjects in the control group are not given instructions on how to structure their daily routine but are still asked to complete the diary. At least one telephone appointment is made for the time the subjects fill out the diaries to maintain compliance. After 4 weeks, there will be a final personal appointment where the diaries will be collected, all questionnaires will be repeated, and blood will be drawn again.

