### Control Group

The control group follows the same conceptual procedure and sequence as the intervention group (Figure 1). Thus, they have the same number of individual sessions and accordingly receive same attention from the study staff. They also fill out all the questionnaires, give blood, and fill out the diary for the same amount of time. However, there are differences in the content of the sessions, in that the control group will not receive information about the circadian clock, its connection to addiction, and the importance of having a structured daily life. Instead, participants of the control group are given the opportunity to discuss, for example, the role of legal drugs, such as alcohol, in society and the effects of alcohol advertising and its impact on both individual and societal consumption behavior. Since the test persons of the control group do not receive any further instructions for the diary and are only asked to fill it in carefully, the evaluation of the study data provides the possibility to compare Routine Variability Scores of test persons of the intervention group and the control group.

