## Measured Outcomes

Our primary hypothesis is that a regular exposure to *Zeitgebers* stabilizes circadian behavioral rhythms and thereby reduces the risk of alcohol relapses in AUD patients. Therefore, the first primary outcomes of the study are the Routine Variability Score and drinking behavior of each individual test person. For generation of the Routine Variability Scores, first, day-to-day variability will be calculated from the following parameters: bedtime, wake-up time, sleep quality, time of getting-up in the morning, time to go to bed in the evening, lights-off time, breakfast time, lunch time and dinner time. The individual Routine Variability Score is comparable to the validated social rhythm metric scale (SRMS) (66) and will be calculated as follows (example for bedtime): For the period of 1 week, the average bedtime will be calculated. Then the deviation from this average bedtime is calculated in minutes for each day. These deviations are summed up and the mean value is calculated. This mean value will be coded according to the magnitude of time variability: 1: 0–15 min, 2: 16–30 min, 3: 31–45 min, 4: 46–60 min, 5: 61–75 min, 6: 76–90 min, 7: 91–105 min, 8: 106–120 min, 9: 2–3 h, 10: 3–4 h, 11: over 4 h (67). This way a separate score can be created for each parameter collected in the diary. These scores can be calculated on a weekly basis to examine whether relapses or deterioration in well-being are related to irregularities in the daily routine during that week, or over the duration of the entire survey phase to check how regularity over a longer period is related to drinking behavior and well-being. In addition, the scores for sleep and meals, for example, can be calculated individually to examine their influence on drinking behavior and well-being separately.

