Additionally, a questionnaire specially designed for this study with a total of 30 questions and a 4-step ordinal scale for the answers to assess the rating of the participants' subjective structuredness in their everyday life will be filled out. This questionnaire includes, for example, questions on the subjective assessment of whether activities such as eating, sleeping and sport are carried out regularly, whether relapses are associated with irregular daily routines, and whether the craving for alcohol usually occurs at the same time of day. To give the subjects of the control group no indication of the actual aim of the study, the questions that aim at the circadian daily structure are mixed with neutral questions.

Drinking behavior and daily craving will be assessed with questionnaires and the diary, respectively (Table 1). General drinking habits of the last few weeks are surveyed using the AUDIT questionnaire. In addition, the European Addiction Severity Index (EuropASI) is used, which covers not only alcohol and drug consumption but also physical, psychological, financial, and social problem areas of addicted patients. The number of alcoholic drinks and the number of alcohol-free days within the past 30 days is assessed by means of the Timeline Followback 30 (TLFB-30). The diary, which the subjects fill out to collect the Routine Variability Scores, additionally records the highest craving for alcohol on a scale of 0–10 of each day.

According to our secondary hypothesis that the stabilization of circadian rhythms contributes to the reduction of depressive symptoms and increased well-being, changes in the affective state, with a focus on depressive symptoms, are measured with the external assessment questionnaire Hamilton Depression Scale (HAMD) and with the self-reporting questionnaire Inventory of Depressive Symptomatology (IDS-SR). Sleep quantity and quality will be assessed by Pittsburgh Sleep Quality Index (PSQI). Furthermore, for measuring if the DAILY structure program will influence the feeling of self-efficacy, we will employ the Generalized Self-Efficacy Scale (GSES).

As exploratory outcomes, it will be documented how many subjects in the DAILY intervention group and the control groups discontinue the therapy. Furthermore, possible changes of the chronotypes in the course of the study will be defined by the Munich ChronoType Questionnaire (MCTQ).

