### Limitations

At this state, however, DAILY has some limitations as it is designed as a pilot study and so, it aims primarily at proofing the principle study concept and the overall impact of a daily structure therapy in AUD patients. A limitation of the current design is that it does not include objective physiological and behavioral measures of circadian rhythm improvement such as (e.g., melatonin rhythms or actigraphy, but only focuses on more subjective behavioral rhythms based on diary entries). However, the primary aim of this pilot study is the proof whether a therapeutic approach to improve sleep hygiene and regularity in daily routine can generally improve AUD symptoms.

Furthermore, inpatients and semi-inpatients are included into our study. Inpatients and semi-inpatients usually already have a more structured daily routine than outpatients since they are given a regulated daily structure by the clinical routines and the fixed therapy hours. Therefore, the determination of individual circadian preferences and characteristics might be limited. However, in our clinic, where the study is currently taking place, patients have no mandatory eating or sleeping hours and can leave the ward and day clinic outside therapy hours. Thus, the test persons can in principle follow their own rhythms, which is often taken advantage of, especially for food and snacks in the surrounding areas. Nevertheless, many test persons report that they generally have more structured daily routines in the clinic than at home, as they adapt to the rhythms of their fellow patients as well as the rhythms of the clinic meals offered.

Furthermore, there are also test persons who, after detoxification or after their stay in the day clinic, go for further treatment to other clinics where they are integrated into a daily structure. Since this daily structure does not necessarily correspond to the subject's circadian characteristics, the analysis of pilot data must consider that these test persons cannot always independently follow the daily schedule during the study. Accordingly, it is possible that the implementation of the DAILY program is more suitable for clinics from which patients are usually discharged home.

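### Planned times are handwritten on the diary pages of the DAILY arm only, so the between-arm comparison of the Routine Variability Score is at risk of measurement bias, most likely in favour of DAILY

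*Protocol article*

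**What the plan says.** The protocol article names two kinds of primary outcome: "the first primary outcomes of the study are the Routine Variability Score and drinking behavior of each individual test person". The score comes from self-completed entries: "The diary, which the subjects fill out to collect the Routine Variability Scores". Measured Outcomes builds it, with bedtime as the example, from a weekly average: "Then the deviation from this average bedtime is calculated in minutes for each day". The mean deviation is then coded from 1 (0–15 min) to 11 (over 4 h), so a lower score means a more regular routine.

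The pages are prepared differently by arm. For the four-week application phase in DAILY, the Week 2 section says: "The times of the designed daily structure plan are handwritten in the empty diary pages as a visual support for precise adherence to the times". In the other arm, the legend to Figure 1 says: "Subjects in the control group are not given instructions on how to structure their daily routine but are still asked to complete the diary". The Control Group section adds that the test persons of the "control group do not receive any further instructions for the diary and are only asked to fill it in carefully", and presents this as what allows the scores of the two arms to be compared.

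The section on weeks 3–6 says the diary also serves self-monitoring and compliance. Under Limitations the article concedes that the design has no actigraphy or melatonin measure and "only focuses on more subjective behavioral rhythms based on diary entries". It does not mention that the pages differ between arms.

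**The concern.** A DAILY patient in weeks 3–6 records actual times on a page that already shows the target times. A control patient, as far as the text allows one to infer, does not. A patient who copies the target, rounds to it, or fills in missed days from it produces a more regular record without having lived more regularly. Only one arm has this prompt.

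The conditions make this plausible. DAILY patients are repeatedly reminded to adhere, early return of completed diaries is optional, and the Outlook section says diaries carry a high risk of non-compliance and data gaps.

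The score tests the first half of the primary hypothesis, that the programme stabilises daily rhythms. It is also the independent variable in the regressions planned under Data Analysis, which pool patients regardless of group. Reporting error that differs by arm would enter those models too.

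**Working it through.** The protocol gives no sample size, variability or expected difference for the score, so there is no stated figure to reproduce. The check asks which way copying moves the score and how far it could.

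**Direction, by hand.** Read the deviation as absolute, since signed deviations from a mean sum to zero. Suppose seven bedtimes lie at −90, −60, −30, 0, +30, +60 and +90 min around the patient's own mean.
- As lived: 360/7 = 51.4 min, code 4.
- The ±30 entries replaced by a planned time equal to the mean: 300/7 = 42.9 min, code 3. The score improves with no change in behaviour.
- The middle entry replaced by a planned time 120 min later: the new mean is 120/7 = 17.1, the absolute deviations sum to 462.9, and 462.9/7 = 66.1 min, code 5. The score worsens.

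The direction therefore depends on how far the plan lies from actual habits. If every entry is copied, the deviation is zero wherever the plan lies.

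**Expected deviation.** For normally distributed times with SD 60 min over 7 days, the mean absolute deviation is 60 × √(2/π) × √(6/7) = 44.3 min. With 20% of entries copied, simulation gives 37.9 min if the plan is at the patient's mean, 44.4 if it is 60 min off, 49.7 if 90 min off and 55.3 if 120 min off. On the 1–11 scale, with the plan at the mean, the average score falls from 3.45 to 3.24 (10% copied), 2.92 (25%) and 2.32 (50%).

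**False-positive rate with no true difference.** The assumptions below are not in the protocol unless a source is given.
- Patients per arm: Study Population gives 3–5 patients at a time and Design gives recruitment within the year. At six weeks each, 3 × 52/6 = 26 and 5 × 52/6 = 43 patients, so 13–22 per arm if allocation is equal.
- Daily SD: 60 min, varying between patients on the log scale with SD 0.3 (narrow) or 0.5 (wide).
- Six clock-time items over four weeks, compared by t-test at 0.05. Measured Outcomes lists eight clock times plus sleep quality; using eight items changes the rates little.
- Plan offset from the patient's usual time: none, or random with SD 30 or 60 min.

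| Between-patient spread, plan offset | 10% copied | 20% copied | 30% copied |
|---|---|---|---|
| Narrow, none | 9–11% | 20–38% | 51–75% |
| Narrow, SD 30 min | 7–8% | 15–22% | 33–52% |
| Narrow, SD 60 min | about 5% | 4–6% | 7–12% |
| Wide, none | 8% | 12–15% | 21–33% |
| Wide, SD 30 min | 5–6% | 8–11% | 13–25% |

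Ranges run over 13 to 22 per arm. With no copying the rate is 4–5%. In the first row the mean deviation falls from about 46 min to about 43, 40 and 36 min. A repeat of the simulation agreed with these rates to within a few percentage points.

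**The case against.** The visual cue is a deliberate part of the treatment, and a real gain in regularity from it is an intended effect. That stands, but the cue need not sit on the recording page, where real and copied regularity cannot be told apart.

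A reader might infer that the score is biased towards benefit and is measured on a different instrument in each arm. The documents support neither. The direction is likely, not certain: the Week 2 section makes the plan a compromise with social constraints and foresees discrepancies of more than 2 h from endogenous preference, and a plan far from actual habits can push the score the other way under partial copying. The instrument is the same diary with arm-specific pre-entries. Its layout (Supplementary Table 1) is not shown, so whether the targets sit in the answer fields or beside them is unknown. The text also does not say that every scored item is pre-written, and the absence of target times on control pages is an inference.

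The study is a pilot not primarily meant to prove treatment success, it discloses that its diary data are subjective, and it defers actigraphy to later work. This lowers the severity. But the disclosed limitation applies to both arms alike, whereas this one differs by arm. The pilot also still plans between-group tests at 0.05 and is meant to inform a main trial. The structuredness questionnaire and the Munich ChronoType Questionnaire are collected outside the diary, but both are self-reports and neither is an objective check.

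**Conclusion.** The concern holds as a risk of bias created by a stated procedure. It should be fixed, but it does not invalidate the trial. The bias most likely favours DAILY, particularly when the plan lies close to the patient's usual times.

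Its size cannot be determined from the protocol. The range of about 5% to about 75% rests on assumed copying rates, daily variability, between-patient spread, plan offset and sample size. The upper end needs 30% copying, a plan at the patient's own mean, a narrow spread and the larger sample, and should not be quoted without those conditions. The lower end applies when the plan is well away from usual times, or when little is copied and patients differ widely.

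Drinking behaviour measured by AUDIT, EuropASI and Timeline Followback does not pass through these pages and is not affected by this mechanism.

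**What to change.** Keep the plan as a visual aid on a separate sheet or card, and issue identical unmarked recording pages in both arms. This costs one extra sheet per patient, a one-line change to the procedure and slightly less convenience for the patient. It reduces the risk without removing it, because DAILY patients still know their target times and have been taught that regularity is the aim.

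For patients already enrolled, record that their pages were pre-written, report the score difference as self-reported regularity, and state the between-arm page difference as a limitation. An analysis with and without these patients should not be relied on: under the current procedure every DAILY patient past the planning session has pre-written pages, so excluding them would remove that arm's data to date, and any later comparison would be between cohorts.

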#### Weeks 3–6: Self-Employed Application of the Daily Structure Plans, Telephone Appointment, and Final Assessment

Starting from this point in the study, the test persons are asked to independently implement the previously developed daily plan for the next 4 weeks and to continue filling out their diaries. The implementation of the daily structure plan can already start at times when the patients are still on the ward or in the day clinic, as patients are allowed to choose the times of all activities (going to bed, eating, leisure activities) freely, with the exception of the fixed therapy sessions on weekdays (see above). However, many patients are discharged or transferred to another institution at different times during this phase of the study. Patients who are discharged home will be asked to follow up the daily schedule outside the clinical setting. Patients who continue their treatment in other institutions will be asked to maintain their daily schedule as much as possible in their new environment. During this time, they can contact the study staff for further assistance (i.e., to adjust the daily structure plan). After 2 weeks, participants are contacted by the study staff by telephone. The telephone call follows the rules of motivational interviewing (65) in order to motivate and remind the participants to further keep to the agreed daily structure and to continue to fill in the diaries thoroughly. If desired, patients are asked to send already completed diaries by fax, mail, or email. The continuous completion of the diary during the application phase of the study serves not only for continuous data collection but also for self-monitoring and increasing compliance. Another 2 weeks later, a last individual appointment is arranged. During this session, diaries will be collected, the questionnaires from the first session are repeated and another blood sample is taken (Table 1).

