### Study Population

Men and women, unemployed and employed subjects are equally included in the study. Depending on whether the subjects are patients of the ward or day clinic, they are in detoxification or post-detoxification treatment. Study enrollment of subjects who are newly admitted to the detoxification program of the ward will take place at the earliest after 5 days of detoxification, to exclude cognitive and physical limitations caused by acute intoxication and its after-effects. Study participants who are discharged from the ward either go home, receive further treatment in the day clinic, or go to other institutions for long-term therapy. Study participants who are discharged from the day clinic either go home after discharge or go to other institutions for further treatment. The health conditions of all test persons allow them to perform their daily tasks without external assistance. Approximately half of the study subjects have a regular job, while the others are unemployed or retired. Usually 3–5 subjects are involved in the study simultaneously.

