### Outlook

In future studies, the determination of individual circadian traits will be optimized in two approaches. First, outpatients will be included because these patients most likely organize their day following primarily their endogenous clock compared to inpatients who are integrated into the daily structures of the clinic. Second, we will also use actigraphy on the one hand to receive a more objective measure of regularity of rest-activity rhythms and on the other hand because filling out diaries carries a high risk of non-compliance and therefore a high risk of data gaps.

In recent years, great progress has been made in the development of machine learning methods for the evaluation of circadian variables of actimeter data, with which for example the circadian phase can be determined (80–83). In this regard, a newly developed DLMO prediction model based on actimetry data, which can be used to quantify circadian misalignment, seems particularly useful to quantify irregularities in circadian rhythms and behavior (84). Therefore, the application of actimeters and the use of mathematical algorithms for analysis will be part of future and more comprehensive studies. The results obtained can in turn be used to adjust and refine daily structure plans of the individual participants of our second study cohort.

Beyond that, we will try to identify times of the day when alcohol cravings are particularly high. Knowing about these times, we will encourage the patients to use these hours to have recourse on learned skills (doing sports, contacting close persons etc.) in order to overcome this period more successfully.

The overall goal of this and more extended future studies is the development of an accompanying therapy for AUD patients that is uncomplicated in its use and easy to implement in the clinical routine. This therapy should enable AUD patients to bring more regularity and structure into their everyday life and thus to strengthen their circadian system. This, in turn, may be a critical component in overcoming alcohol withdrawals and in preventing relapses more successfully.

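### The four-week plan-phase diaries have one scheduled collection point and earlier return is voluntary, so a participant who neither attends nor sends pages has no observed plan-phase Routine Variability Score

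*Protocol article*

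**What the plan says.** Under Measured Outcomes, "the first primary outcomes of the study are the Routine Variability Score and drinking behavior of each individual test person". The score comes from diary times. Its unit is the week ("For the period of 1 week, the average bedtime will be calculated") and the section adds: "These scores can be calculated on a weekly basis". Daily craving is recorded in the same diary.

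There are two diary periods. The test diary is reviewed early; according to the Figure 1 legend, "After at least 1 week, the diary is evaluated". New blank diaries are then issued for four weeks (Week 2 section). For those, the Figure 1 legend says "there will be a final personal appointment where the diaries will be collected", and the Weeks 3–6 section repeats this. The telephone call halfway through is there to motivate and remind. On earlier return, the Weeks 3–6 section says only: "If desired, patients are asked to send already completed diaries by fax, mail, or email".

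The same section expects many patients to leave the clinic or move elsewhere during this phase, and Study Population says that some will "go to other institutions for long-term therapy". The Outlook concedes that "filling out diaries carries a high risk of non-compliance and therefore a high risk of data gaps". Data Analysis keeps everyone who has the first-session questionnaires and the first diary week, and fills gaps by imputation from whatever was assessed up to that point.

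**The concern.** A primary outcome depends on paper that the participant holds for four weeks, in a population that the authors expect to disperse during those weeks. Two things are at stake.

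- **Avoidable and possibly informative loss.** Weeks that were filled in but never handed over count as missing. Missing the last visit is plausibly tied to relapse or transfer. It may also differ by arm, because Study Hypotheses and Objectives expects more participants to complete under DAILY than under control. The imputation cannot restore what was lost, since the only regularity data left come from before the plan existed.
- **Late completion that may act differently by arm.** The Week 2 section has the planned times handwritten on the intervention arm's blank pages. The control arm has no plan. Someone in the intervention arm who fills in pages shortly before the visit has target times to copy, and copied times score as highly regular. A control participant has nothing comparable to copy.

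**Working it through.** The article gives no sample size, dropout rate or attendance rate, so there is no planned figure to reproduce. The check is a count of diary days.

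**Inputs.** Test diary: at least 1 week, taken as 7 days (Figure 1 legend). Plan phase: 4 weeks, 28 days (Week 2 section). Telephone call: after 2 weeks, that is after 14 plan-phase days (Weeks 3–6 section). Scoring unit: 1 week (Measured Outcomes).

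**Share of diary data that depends on the final visit if nothing is sent.** 28 / (7 + 28) = 28/35 = 80% of all diary days, and 28/28 = 100% of plan-phase days. If the test diary runs longer than 7 days, the 80% falls; the 100% does not change.

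**Loss for one participant who fills in all 28 days and then misses the visit:**

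| Pages sent before the visit | Plan-phase days lost | Weekly scores kept |
|---|---|---|
| None | 28/28 = 100% | 0 of 4 |
| At the 2-week call | 28 − 14 = 14; 14/28 = 50% | 2 of 4 |
| Weekly, last week outstanding | 28 − 21 = 7; 7/28 = 25% | 3 of 4 |

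**Trial level, assumption only.** Let p be the proportion who miss the visit and send nothing afterwards, with p from 10% to 40%.

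- No early return: a proportion p has no observed plan-phase score, 10% to 40%.
- All have sent pages at the 2-week call: p × 14/28 = 5% to 20% of plan-phase days missing, and everyone keeps two weekly scores.
- All have sent pages weekly: p × 7/28 = 2.5% to 10% of plan-phase days missing.

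**What imputation can use.** For a participant with no plan-phase pages, the diary data assessed up to dropout are the test week. That week precedes the daily structure plan. Imputing from it tends to pull the plan-phase score towards the pre-plan level, which would shrink a true difference between arms. Copying planned times on late pages works the other way and would enlarge the difference. The two need not cancel, and the article gives nothing from which to size either.

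**The case against.** Much can be said on the other side, and part of it stands.

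- *The remote route exists.* A reader might infer that every diary stays with the participant until the last visit, and that anyone who misses it loses the whole outcome. The text does not support that. Fax, mail and email are offered, weeks already sent can be scored, nothing bars posting pages later, and the test week is already with the study. The total loss applies only to those who neither attend nor send anything. Such participants also remain in the analysis through imputation, and drinking behavior, the other first primary outcome, is measured mainly by questionnaire.
- *Both arms follow the same procedure.* Because optional return is described under the intervention group, a reader might infer that controls are not offered it. The opening of Study Procedure and the Control Group section say that procedure and sequence are shared, so this inference fails.
- *Back-filling might be detectable.* The diary form (Supplementary Table 1) and the full protocol are not shown. One can say that the article describes no check on the time of entry, not that none exists. Nor does the article support a general claim that reconstructed times are smoother than true ones. The narrower point about handwritten plan times rests on its text.
- *The authors disclose the weakness.* The Limitations section and the Outlook acknowledge the reliance on diaries and the risk of gaps, and actigraphy is deferred to later studies. This is fair for a pilot, but disclosure does not recover pages that could have been collected.
- *Logistics belong in the full protocol.* Silence on receipt logs is indeed no fault in a condensed article. The point here is a stated procedure: one scheduled collection, with earlier return left to choice.
- *Weekly return also needs compliance.* True. Those who later drop out may not send pages either, so the reductions shown are the best case.

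**Conclusion.** The concern holds in limited form. The article schedules a single collection of the plan-phase diaries and leaves earlier return to the participant. For someone who neither attends nor sends pages, 28 of 28 plan-phase days are unobserved, and the imputed score rests on pre-plan regularity data. That this loss relates to relapse or transfer, and differs by arm, is plausible from the authors' own expectations but is not shown. The possible bias in favour of DAILY depends on late completion actually happening and going unchecked, and the article settles neither.

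The number of patients affected cannot be given. A reader might take the 3–5 concurrent participants in Study Population over one year of six-week cycles (3 × 52/6 = 26; 5 × 52/6 ≈ 43) and assume 20–40% non-attendance, giving about 5 to 17 patients (0.20 × 26 = 5.2; 0.40 × 43 = 17.2). Neither input is stated as such a figure, and the result also requires that nobody sends pages early or late, so it should not be cited.

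This does not invalidate the trial. It is an inexpensive improvement to a primary outcome and worth making.

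**What to change.** In the Weeks 3–6 section, replace the optional wording with routine return of completed diary pages, stated explicitly for both arms:

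1. Ask for completed pages at least at the existing 2-week call, and preferably every week, by the routes already offered.
2. Log the date on which each page is received.
3. Ask participants who do not attend the final appointment to send their remaining pages by the same routes.
4. Define in advance when a page counts as late, for example when it arrives after the next return was due. Run a sensitivity analysis of the Routine Variability Score that excludes or flags late pages, by arm.

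The cost is slightly more effort for participants and a receipt log. No new visit or assessor is needed. The log also gives the pilot a by-arm record of diary return and timeliness for planning the main trial.

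Do not extend postal return to the questionnaires. At baseline they are filled out together with the participant (Informed Consent and Baseline Assessments), so posting them would change the mode of administration for a selected subgroup.
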